### Statistical analyses

Initial descriptive analyses will be performed for all variables measured in the study, both quantitative (mean and standard deviation) and qualitative (frequencies and percentages). Normality tests will then be conducted to determine the appropriate statistical tests for specific analysis. Subgroup analysis will be performed: treatment x sex interaction [31]. A significance level of 5% probability or corresponding p-value will be adopted for all tests. All analyses will be conducted using the statistical software SPSS for Windows, version 9.1. Interim analysis was not planned.

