## Abstract

Photobiomodulation is a safe option for controlling pain, edema, and trismus when applied postoperatively in third molar surgery. However, administration prior to surgery has been under-explored. This study aims to explore the effectiveness of pre-emptive photobiomodulation in reducing postoperative edema in impacted lower third molar extractions. Two groups of healthy individuals undergoing tooth extraction will be randomly assigned: Control group receiving pre-emptive corticosteroid and simulated photobiomodulation, and Photobiomodulation Group receiving intraoral low-intensity laser and extraoral LED cluster application. The primary outcome will be postoperative edema after 48 h. The secondary outcomes will be pain, trismus dysphagia, and analgesic intake (paracetamol). These outcomes will be assessed at baseline as well as two and seven days after surgery. Adverse effects will be recorded. Data will be presented as means ± SD and a p-value < 0.05 will be indicative of statistical significance.

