### Sample size calculation

The sample size was calculated to provide an 80% power (α = 0.05). The sample size will consist of 30 surgeries per group. Thirty patients with bilateral and symmetric lower third molars (right and left) will be selected. The procedure will then be performed randomly (split-mouth design), totaling 60 surgeries (30 surgeries in the control group and 30 surgeries in the experimental group). For the calculation, we used the 48-hour time point in the article by Aras and Güngörmüş (2010) [21]. The average edema measurement was 105 mm in the control group and 109 mm in the experimental group. The larger standard deviation between the two means ±5 mm was chosen for the sample size calculation.

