### Randomization

We will use a random sequence generator program (https://www.sealedenvelope.com/) to assign participants to the two experimental groups. Randomization will involve 30 participants. Each participant will undergo two surgeries–one on each side. The first surgery will be performed on the right side and treatment for the left side will be the opposite of the randomized treatment, ensuring no repetition of identical treatments in the same patient. A third party not otherwise involved in the study will handle sequence generation and envelope preparation. Opaque envelopes labeled with sequential numbers will contain a sheet specifying the group for the first surgery based on the generated sequence. These envelopes will remain sealed and stored securely in numerical order until the surgeries.

The patients will undergo assessments by the surgeons and, upon meeting the previously described eligibility criteria, will be enrolled in the study. All participants will be submitted to the same surgical protocol. Just prior to the surgeries, the researcher responsible for photobiomodulation application will open an envelope (without changing the sequence of the remaining envelopes) and perform the procedure indicated.

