### Study outcomes

The primary outcome of the study will be:

Edema—three measurements will be taken on the patient’s face with a previously sanitized flexible measuring tape: tragus-pogonion, tragus-labial commissure, and mandibular angle-outer orbital commissure [26]. Measurements will be taken immediately before surgery as well as two and seven days after surgery.

The secondary outcomes of the study will be:

Pain Sensitivity*—*The visual analog scale (VAS) is the most widely used instrument for measuring postoperative pain after oral surgeries with photobiomodulation in the postoperative period [24, 26]. In this study, the VAS will be used immediately after surgery as well as two and seven days after surgery [24, 26] using 10-cm line with "0" (no pain) at one end and "10" (unbearable pain) at the other. Instructions on marking will be provided to the patient by the same operator.

Quantity of pain tablets taken during the period*—*The number of analgesic tablets taken at two and seven days will be counted. All participants will take paracetamol and be instructed to take it every six hours only in the presence of pain [27]. At the beginning of the study, each participant will be provided a paracetamol tablet, which is a drug with purely analgesic effects [28]. At the end of the experiment, the quantity of tablets will be evaluated as a secondary outcome. Patient adherence will be monitored. For such, the patients will be asked to bring the medication blister pack to the appointment to check how it is being used.

Postoperative trismus assessment*—*Spasms in the masticatory muscles (trismus) can limit or even prevent mouth opening after the surgical removal of impacted third molars [21, 23, 29]. This outcome is typically evaluated by measuring the distance between the incisal edges of the upper and lower central incisors using calipers [27, 29]. In this study, previously calibrated evaluators will measure mouth opening in each patient before surgery as well as two and seven days after surgery.

Impact of the surgical procedure on quality of life*—*Two previously calibrated evaluators will ask patients to respond with "yes" or "no" to the following 10 questions two and seven days after surgery, as described by Sierra et al. (2013) [26] and Sierra et al. (2015) [24].

The 10 questions were:

Are you maintaining your social activities normally?

Are you working/studying normally?

Are you maintaining your regular diet?

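### Normality tests on the trial data are to choose the primary test, and the plan nowhere states that it will use the within-patient pairing or the pre-surgery edema value

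*Protocol article*

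**What the plan says.** **Choice of test.** Protocol article, Statistical analyses: after descriptive statistics, "Normality tests will then be conducted to determine the appropriate statistical tests for specific analysis". The section adds a sex-by-treatment subgroup analysis, a 5% level and the software. It names no primary test, patient effect, side or order term, change score or baseline covariate.

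**Design.** Sample size calculation: "The procedure will then be performed randomly (split-mouth design), totaling 60 surgeries (30 surgeries in the control group and 30 surgeries in the experimental group". Randomization: the right side is operated on first, and "treatment for the left side will be the opposite of the randomized treatment, ensuring no repetition of identical treatments in the same patient". Each patient is therefore their own control.

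**Wording that points to independent groups.** The Abstract has "Two groups of healthy individuals undergoing tooth extraction will be randomly assigned". The sample size section takes two group means from a cited study (105 and 109 mm) and the larger group SD (5 mm). It gives no SD of within-patient differences and no correlation.

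**Edema data.** Study outcomes: three facial distances, and "Measurements will be taken immediately before surgery as well as two and seven days after surgery". Preoperative assessment also calls for a baseline of every outcome. The Abstract sets 48 h as the primary time point.

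**The concern.** A normality test can at most decide between a parametric and a rank method. It cannot decide between a paired and an unpaired method, and in a split-mouth trial that is the choice that matters most. An analyst who took the Abstract's wording and the sample size inputs at face value could pass the normality step and run a two-sample t-test or Mann-Whitney test on 60 surgeries as if they came from 60 people.

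The rule also leaves the primary p-value unfixed until the data are seen. Edema is three distances, so the rule could send them to different tests. It does not say whether normality is judged on the raw values in each arm or on the within-patient differences, and only the differences bear on a paired t-test.

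Raw distances on two sides of one face share that face's size, so a positive correlation is to be expected. Ignoring it would give intervals wider than the data warrant. The comparator is an active corticosteroid, and the Discussion presents photobiomodulation as an alternative. An avoidably wide interval could therefore hide a real difference in either direction.

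**Working it through.** **Inputs.** From Sample size calculation: difference 109 - 105 = 4 mm, SD 5 mm per side, 30 surgeries per group, 80% power, alpha 0.05. Two-sided testing is assumed because the protocol does not state sidedness. The within-patient correlation rho is not given, so it is assumed and a range is shown. The 2 mm difference is used only to illustrate effects smaller than planned and does not come from the protocol.

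**Step 1: the protocol's own figure.** For two independent means, n per group = 2 × (1.96 + 0.84)² × 5² / 4² = 24.5, so 25. The t-test version gives 26. At 30 per group the power is 87% (normal) or 86% (t). The stated 30 is thus not reproduced without an unstated allowance; for example, 25 / (1 - 0.15) = 29.4, so 30. That is a separate documentation gap and does not affect this point.

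**Step 2: standard errors with 30 pairs.**
- Unpaired formula: 5 × sqrt(2/30) = 1.29 mm, whatever rho is.
- Paired formula: SD of differences = 5 × sqrt(2(1 - rho)); SE = that SD / sqrt(30).
- Ratio, unpaired to paired: 1/sqrt(1 - rho).

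| rho (assumed) | SD of differences, mm | SE paired, mm | SE unpaired, mm | Ratio | Pairs for 80% power at 4 mm | Power, 30 pairs, 4 mm |
|---|---|---|---|---|---|---|
| 0 | 7.07 | 1.29 | 1.29 | 1.00 | 27 | 85% |
| 0.3 | 5.92 | 1.08 | 1.29 | 1.20 | 20 | 94.7% |
| 0.5 | 5.00 | 0.91 | 1.29 | 1.41 | 15 | 98.9% |
| 0.7 | 3.87 | 0.71 | 1.29 | 1.83 | 10 | >99.9% |

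At rho 0.5 the 95% CI half-width is about 2.00 × 1.29 = 2.6 mm unpaired (58 df) and 2.05 × 0.91 = 1.9 mm paired (29 df).

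**Step 3: simulated rejection rates** (20,000 trials of 30 bivariate-normal pairs, SD 5 mm, nominal 5%).

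| rho (assumed) | Type I error, unpaired | Power at 2 mm, unpaired / paired | Power at 4 mm, unpaired / paired |
|---|---|---|---|
| 0 | 4.9% | 33% / 33% | 86% / 85% |
| 0.5 | 0.7% | 28% / 56% | 93.4% / 98.9% |
| 0.7 | 0.07% | 23% / 78% | 96.9% / >99.9% |
| 0.9 | 0% | 14% / 99.7% | 99.6% / 100% |

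**Step 4: baseline timing, sections side by side.** Surgical procedures and Experimental design place the irradiation or tablet an hour ahead of the operation. Study outcomes takes the edema measurement just before the operation. Preoperative assessment ties the baseline to the pre-surgery work-up after consent. Blinding of the study and Experimental design attach the word baseline to the irradiation or sham period itself. Together these do not settle whether the measurement comes before or after treatment.

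**The case against.** **No unpaired test is named.** The protocol promises appropriate tests for a declared split-mouth design, and a paired test fits that description. This is a condensed article, and a separate analysis plan may name the test. A reader might infer that the trial has chosen to ignore the pairing and the baseline; the text does not support that. The simulated losses describe an analysis the protocol leaves open, not one it specifies. What remains is that the selection rule is stated in the text and rests on distribution shape alone. A later plan would have to replace that rule, not merely add detail to it.

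**The loss is small at the planned effect.** This stands. At 4 mm both analyses exceed 80% power, and at rho 0 nothing is lost.

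**The statistician is blinded.** Groups are revealed only after the analysis (Blinding of the study). This limits a choice of test that favours one treatment, but it does not fix the primary test in advance.

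**The Abstract is loose wording.** This is largely right, because the Methods make the design clear. The wording matters only because nothing in the analysis section corrects it.

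**The baseline may precede treatment.** A reader might conclude from the Study outcomes wording that the baseline is a post-treatment value. The sections conflict in how they use the term and do not establish that.

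**Conclusion.** The point holds as a should-fix. The protocol lets the trial data select the primary test and nowhere states that the analysis will use the within-patient pairing or the pre-surgery edema value, although the design supplies both.

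If an unpaired test were chosen, its standard error would be too large by 1.41 at rho 0.5 and 1.83 at rho 0.7. Power at 2 mm would fall from 56% to 28% and from 78% to 23% respectively. At the planned 4 mm it would fall only from 98.9% to 93.4% at rho 0.5. These figures assume normal data, an SD of 5 mm on each side and a positive correlation that the protocol does not give. The further gain from adjusting for the pre-surgery value is not quantified, because the protocol gives no figure for it.

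Two stronger readings do not follow. The problem is not an excess of false positives: under positive correlation the error is conservative. Nor is the trial too small: 30 patients exceed the 27 pairs needed for 4 mm even at rho 0.

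**What to change.** 1. Replace the normality step with one pre-specified primary analysis of 48 h edema. Either a paired analysis or a linear mixed model with patient as random effect will serve. Include treatment, a single side/order term (the right side is always first, so side and order are one factor) and that side's own pre-surgery value. Report the photobiomodulation-minus-dexamethasone difference with its 95% CI.
2. Keep a signed-rank or permutation test as a sensitivity analysis only.
3. Use paired methods for the other outcomes, including the ordinal and yes/no ones, and test the sex interaction on within-patient differences.
4. Reconcile Blinding of the study, Preoperative assessment, Surgical procedures, Experimental design and Study outcomes on whether the baseline measurement precedes the tablet or irradiation, so that the status of the covariate is known.
5. Align the Abstract with the split-mouth design.

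The cost is wording and minor programming, with no added patients or visits. If the reconciliation moves the baseline measurement, only its timing on the day changes. The changes should be settled before any outcome data are examined.

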## Discussion

For the management of pain and swelling following third molar extractions, some authors recommend the pre-emptive use of anti-inflammatories. However, conclusive evidence regarding the efficacy of pre-emptive use remains elusive. In a 2018 systematic review addressing optimal dosages and administration routes for corticosteroids in lower third molar extractions, indicated an absence of well-established standards for the ideal route, type, and dosage. Nonetheless, preoperative corticosteroid administration through submucosal injection demonstrated effectiveness in mitigating edema, pain, and trismus post-surgery (Larsen et al., 2018) [10]. In 2019, a meta-analysis found that methylprednisolone, irrespective of administration route, significantly alleviates immediate postoperative edema, albeit with no discernible impact in the subsequent days following lower third molar extractions. Oral administration or intra-masseter application appeared promising in reducing pain and trismus during the immediate postoperative period. Notably, oral administration demonstrated potential in mitigating late-phase pain, while intra-masseter administration effectively controlled trismus. Despite these findings, researchers underscored the imperative for additional controlled and randomized clinical trials to fortify evidence pertaining to methylprednisolone prescription in lower third molar extractions [12]. A 2019 systematic review with meta-analysis concluded that corticosteroids exhibit greater efficacy than placebos in managing pain and trismus associated with the postoperative period of lower third molar extractions, particularly when employed preventively or pre-emptively. The route of administration minimally influenced outcomes, except for the submucosal route. Continuation of corticosteroid use post-surgery did not yield additional positive effects in postoperative comfort [13]. Nevertheless, a 2021 systematic review with meta-analysis by Singh et al. [14] indicated that the use of systemic corticosteroids, even in oral surgeries involving trauma, rests on weak scientific evidence, necessitating further studies to substantiate its recommendation.

Photobiomodulation (PBM) has emerged as a viable alternative for postoperative management in third molar surgeries, effectively controlling pain, swelling, and trismus [17, 18]. Two studies have highlighted the preventive efficacy of PBM, specifically with infrared wavelength, in lower third molar extractions [19, 20]. However, the combined preoperative application of PBM has not been explored to date. Considering the positive outcomes observed with PBM, it is plausible that pre-emptive application using both red and infrared LED, both extraorally and intraorally, could prove effective in reducing postoperative swelling in lower third molar extractions. Consequently, PBM stands as a non-pharmacological alternative to enhance postoperative comfort following impacted lower third molar extractions.
